# Mckenzie therapy plus simplified Wuqinxi exercise for improving lumbar spine motor function in chronic low back pain: a randomized controlled trial protocol

**DOI:** 10.3389/fspor.2026.1807993

**Published:** 2026-05-07

**Keywords:** chronic low back, combined therapy, McKenzie therapy, traditional martial arts, Wuqinxis

## Abstract

**Background:**

Chronic low back discomfort may result in functional restrictions that can be incapacitating and cause disruptions to family life. McKenzie therapy (MT) can reduce pain by improving the functional structure of the lumbar spine through exercise and posture, while the simplified Wuqinxis (WQXs) can play a dual role in adjusting physical form and mental state as a traditional Chinese medicine exercise. This study aims to combine the concepts of the two therapies, to develop a more effective and easy exercise prescription for the prevention and treatment of lower back pain, and to explore the biomechanical effects and clinical efficacy.

**Methods and analysis:**

A randomized controlled trial will be conducted to compare the efficacy of WQXs with or without MT on patients with chronic low back pain. A total of 74 patients will be randomly assigned to an experimental group (MT and WQXs) and a control group (WQXs). Lumbar range of motion and health-related quality of life in patients with chronic low back pain will be assessed using the range of motion scale, visual analogue scale, and the SF-36 scale. Additionally, surface electromyography (sEMG) and isokinetic muscle strength testing will be employed to evaluate the mechanical properties of the core muscles in the lumbopelvic region. Consider a 20% dropout rate, 74 cases will be gathered in total, taking into account a 20% dropout rate.

**Results:**

to ascertain whether the exercise prescription combining the two therapies is effective for treating chronic low back pain.

**Clinical Trial Registration:**

Chinese Clinical Trial Registry, identifier ChiCTR2300075499.

## Strengths and limitations of this study

This is a small-scale randomized controlled trial investigating the effects of active exercise combined with passive physical therapy on lumbar mobility, pain, and quality of life.This integrated approach, which combines Eastern and Western therapeutic modalities, may offer a novel paradigm for enhancing the rehabilitation of patients with chronic lower back pain.The outcomes will provide crucial insights related to lumbar spine functionality, encompassing aspects of pain, range of motion, and capabilities in daily living.This study is characterized by a modest sample size, necessitates further validation through the acquisition of additional data.

## Background

1

Low back pain (LBP) constitutes a pervasive condition, exerting its impact on individuals spanning the entire globe (1), which includes three primary components: axial lumbosacral pain, radicular pain, and referred pain. Axial lumbosacral pain encompasses the lumbar region (L1-5 vertebral level) and sacral region (S1 to sacrococcygeal junction). Radicular pain arises from nerve or dorsal root ganglion distribution into the extremities along the dermatomal pathway, while metastatic pain refers to pain that emanates from a distant source along the non-cutaneous trajectory. All the three types of LBP are prevalent worldwide (2, 3) and can significantly impair patients’ quality of life (4).

LBP is also classified by symptom duration: acute (<6 weeks), subacute (6–12 weeks), or chronic (>12 weeks) (5, 6). Evidence suggests that approximately 20% of patients with acute low back pain progress to chronic back pain over time (7). In developed countries, treatment for chronic LBP costs at least one million dollars annually (8). This has resulted in high medical expenses and loss of productivity, posing significant socioeconomic challenges (9). As a result, understanding the underlying mechanisms, optimizing treatment strategies, and improving clinical outcomes for chronic LBP have become increasingly complex and critical priorities for healthcare professionals.

Treatment of chronic LBP is multifactorial, involving physicians, patients, families, and society. Chronic low back pain (CLBP) exhibits a high incidence among young adults and middle-aged individuals. As this age group constitutes the primary labor force, they demonstrate substantial rehabilitation needs (10). Approximately one-third of low back pain patients experience moderate discomfort. Patients tend to avoid opioid analgesics unless their pain is severe and fails to respond to more conservative medications (11). Psychosocial and emotional factors play a significant role in the prognosis and persistence of chronic LBP (12). The National Institute for Health and Care Excellence (NICE) (13) recommends early management and treatment of chronic lower back pain through information, education, patient preference, regular exercise, and physical activity. NICE also endorses Mckenzie therapy (MT) for individuals with LBP. Manual therapy entails neurophysiological interventions such as reducing inflammation, decreasing spinal excitability and pain sensitivity, altering the activity of cortical areas involved in pain processing, and stimulating the sympathetic nervous system (14, 15). While MT offers a personalized treatment approach for chronic LBP, its overall clinical efficacy remains a subject of debate (16, 17).

The WQXs was created by Hua Tuo, which is renowned as a famous doctor in Chinese history (18), This mind–body practice imitates the movements and breathing patterns of the five animals: tiger, bear, crane, monkey, and deer, and integrate breathing postures and movements, which can lessen stress on the injured ligaments of the lumbar spine, alleviate pain, and improve function (19–22). Furthermore, low-load lumbar multilevel isometric exercises, such as those embedded in WQXs, have been shown to enhance spinal control and stability (23–25). Both the McKenzie Method and Wuqinxi are applicable to patients with non-specific low back pain (NSLBP). Furthermore, both interventions possess a solid foundation of clinical application across different age groups. But the efficacy of the combination of WQXs and MT, an active movement combined with a passive rehabilitation therapy, is yet to be determined. This study aims to conduct a small randomized controlled trial to observe the impact of this combination on lumbar spine mobility, pain, and quality of life. A novel treatment program that integrates both approaches will be offered to patients.

## Methods

2

### Design

2.1

All patients are recruited from community residents in the Hongkou and Yangpu districts of Shanghai voluntarily. After obtaining informed consent, they are randomly assigned to either control group or experimental group: control group receive a simplified WQXs intervention, which is refer to as WG, and experimental group receive a combination of simplified WQXs and MT intervention, which is refer to as WMG. The study observation period was 24 weeks. The range of motion (ROM) of the lumbar spine in flexion, extension, and lateral flexion was measured using an electrogoniometer. Pain and the quality of life of patients with chronic low back pain is assessed using scales such as the visual analogue scale (VAS) and the SF-36 questionnaire. The mechanical properties of the lumbago core muscles are evaluated using surface electromyography and isokinetic muscle strength tests to explore the underlying biomechanical mechanisms and enhance clinical efficacy. The following covariates were collected at baseline: age, sex, body mass index (BMI), occupational type (sedentary/manual labor), daily physical activity level, disease duration, and history of low back pain. The impact of these factors on low back pain was analyzed (Figure 1).

**Figure 1 F1:**
[figure not shown]
Aims and study flow diagram.

**Eligibility criteria**

Inclusion criteria
Volunteers who meet the diagnostic criteria for chronic low back pain;Age between 18 and 60 years old, gender unrestricted, capable of actively participating in treatment;First-time diagnosed patients or those who have not previously received surgical or standard conservative treatments; participants must sign an informed consent form, comply with its terms, and voluntarily agree to take part in this study.**Exclusion criteria:**
Pathogenic factors that contribute to low back pain (symptoms of spinal cord compression, rheumatoid arthritis) are excluded from the diagnostic criteria;Patients with severe cardiovascular and cerebrovascular diseases, metabolic disorders, and mental illnesses;Individuals who have undergone regular physical therapy or other rehabilitation therapies within the past three months.

### Aims and hypotheses

2.2

The primary objective of this study is to elucidate the therapeutic efficacy of WQXs when integrated with passive recovery and vigorous exercise regimens. Investigating the impact of this combination on lumbar mobility, pain, and quality of life to determine whether the combination of MT and WQXs may alleviate persistent lower back pain. It is hypothesized that the integration of these two modalities would lead to improved quality of life, less discomfort, and increased mobility as compared to either modality applied in isolation.

### Participants & recruitment

2.3

Enrollment in this study begins on September 1 5, 2023 and will end upon completion of the required subject enrollment. A plan and methodology for subject engagement was established to help subjects understand the purpose and plan of the trial, which may include the preparation of informed consent forms, collection of necessary data, and visual aids such as videos and pictures. During the recruitment process, the advantages and disadvantages of the experimental treatment will be explained in detail, as well as the safety measures that will be taken during the trial, and the implementation of safety protocols will be guaranteed. In addition, wider publicity will be provided through the distribution of recruitment posters in the community and the use of the Internet. The study team will initially assess the eligibility of each subject based on the inclusion/exclusion criteria, followed by relevant examinations. Subsequently, upon the formal signing of the informed consent form, the participants’ adherence to the inclusion and exclusion criteria will be definitively confirmed based on the outcomes of these assessments.

### Randomization

2.4

Grouping will be done using a computer-generated table of randomized numbers, Random numbers will be assigned by an independent person who will not participate in this study. Random numbers will be placed in opaque envelopes by an independent person who is not involved in this trial to achieve allocation concealment.

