### Sample size

2.10

In this study, the formula for calculating the sample size for the two-sample test of variance was used, with lumbar anterior flexion range of motion as the main effector, and referring to the literature report and the result of the pre-test, the range of motion of lumbar anterior flexion in the two treatment groups was 46.20 ± 5.25 and 42.59 ± 5.14 (26), respectively, which was calculated to require 33 patients in each group. Accounting for an anticipated 10% dropout rate, the total sample size needed is 74 participants.

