### Statistical analysis plan

2.11

According to the Case report form (CRF) table, after each measurement, the data are double-entered into Stata software within one week, and the data are processed and analyzed using SPSS26.0 statistical software. Measurement data are expressed as mean ± standard deviation, and the *t*-test is used if the data meet the normal distribution, and the rank-sum test is used if the data do not meet the normal distribution and the chi-square test was used for comparison of count data. *α* = 0.05 was used as the test level for significant differences.

If there are intolerable or serious adverse reactions during exercise, the trial will be discontinued; however, those who have participated in more than 1 cycle of exercise should be counted for efficacy. Volunteers who are unwilling to continue the clinical trial during the trial and take the initiative to ask the investigator to discontinue the trial could discontinue the trial. In case of discontinuation, more than 1/2 of the data are analyzed and less than 1/2 are excluded.

If imbalances exist between the two groups at baseline regarding variables such as gender, occupation, and physical activity, Analysis of Covariance (ANCOVA) with covariate adjustment will be employed as a sensitivity analysis。

Recognizing that age may influence musculoskeletal elasticity, the speed of rehabilitation response, and compliance, we performed a stratified analysis by age (e.g., <40 years vs. ≥40 years) in addition to conventional analyses, to examine whether there was a significant interaction effect of the intervention across different age groups.

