Therefore, it is very important to combine the MT technique concept with the exercise routines of the simplified WQXs to form a set of more ideal, superior exercise therapies for treating patients with chronic low back pain. But the research direction of this topic combines the concepts of traditional exercise rehabilitation (simplified WQXs) and modern exercise rehabilitation techniques (MT) to formulate an easier and more effective exercise prescription for treating and preventing low back pain while exploring its effects on low back pain and cardiovascular health. This approach aims to improve clinical efficacy while implementing a low-cost, high-efficiency, scientific modern gong method to address a common high morbidity issue and play a positive role. Although this study did not systematically evaluate the participants’ static posture or dynamic postural patterns, the intervention itself incorporated elements of posture correction. This study did not distinguish the independent effects of each intervention factor in the treatment of low back pain. In the future, the sample size should be increased and more subgroups included to investigate the independent effects of each intervention factor. Future research should integrate posture assessment tools (e.g., photogrammetry or motion capture systems) to quantify habitual posture and analyze its association with therapeutic efficacy. Subsequent studies will adopt a multicenter, stratified randomized design to more precisely control for confounding variables.

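### Age is named as a possible influence on response, yet allocation is evidently not stratified by it and the main range-of-motion comparison does not adjust for it

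*Protocol article*

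**What the plan says.** Section 2.4 (Randomization) describes allocation in one phrase, "Grouping will be done using a computer-generated table of randomized numbers", with an independent person and opaque envelopes. It mentions neither blocks nor strata. The Discussion closes with "Subsequent studies will adopt a multicenter, stratified randomized design to more precisely control for confounding variables", which places stratification outside this trial.

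Section 2.11 (Statistical analysis plan) gives its reason for an age analysis as "Recognizing that age may influence musculoskeletal elasticity, the speed of rehabilitation response, and compliance". It then describes an analysis by age band to look for an interaction with treatment. The 40-year cut is offered only as an example.

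For the comparison itself, 2.11 uses a t-test for normally distributed measurements and a rank-sum test otherwise. If baseline variables are out of balance, "Analysis of Covariance (ANCOVA) with covariate adjustment will be employed as a sensitivity analysis". The examples given are sex, occupation and physical activity. Age is not named there, although section 2.1 lists it among the covariates collected at baseline.

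**The concern.** The plan names a factor that may act on the very quantity being measured, because elasticity bears on lumbar flexion, and eligibility runs from 18 to 60 years. It then uses that factor neither in the allocation nor in the main test. With 74 patients, the age mix of the two arms can differ noticeably by chance. Whatever part of the range-of-motion difference comes from that gap is then reported as part of the treatment difference.

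The ANCOVA does not close this gap. It is a sensitivity analysis, so the headline result stays unadjusted. It is also run only if imbalance is seen, with no stated threshold, so the use of the adjusted analysis depends on the data. The value of adjustment depends on how strongly age predicts the outcome, which holds whether or not the arms happen to look balanced.

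**Working it through.** **The plan's own figure.** Section 2.10 gives 46.20 ± 5.25 and 42.59 ± 5.14 for lumbar flexion. The difference is 3.61. The pooled SD is √[(5.25² + 5.14²)/2] = 5.195, with variance 26.99. Power is not stated. With two-sided α = 0.05 and 80% power (both assumed), n = 2 × (1.960 + 0.842)² × 26.99 / 3.61² = 32.5, rounded up to 33 per group. Allowing for 10% dropout, 33/0.9 = 36.7, so 37 per group and 74 in total. The stated 33 and 74 reproduce.

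**How large a chance age gap is.** Let f be the share under 40. The article does not give it, so f = 0.30 to 0.50 is assumed. With 37 per arm, the SD of the between-arm difference in that share is √[f(1 − f) × 2/37].

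| f (assumed) | SD of gap | 0.15 / SD | P(gap ≥ 15 points), normal approximation | Same, by simulation |
|---|---|---|---|---|
| 0.30 | 0.107 | 1.41 | 16% | 16% |
| 0.40 | 0.114 | 1.32 | 19% | 19% |
| 0.50 | 0.116 | 1.29 | 20% | 20% |

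The simulated chance of a gap of 20 points or more is about 6% to 9%. The 15-point results are practically the same whether arms are held at 37:37 or left to simple randomisation. Balancing arm size alone therefore does nothing for age mix.

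**What a gap would do to the result.** The article gives no age effect in degrees, so two values are assumed for illustration. The shift in the between-arm difference is the gap times the difference between age bands.

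- Bands differ by 5 degrees (about 1 SD): 0.15 × 5 = 0.75 degrees, and 0.75/3.61 = 21% of the planned difference.
- Bands differ by 2.5 degrees: 0.15 × 2.5 = 0.375 degrees, and 0.375/3.61 = 10%.

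**What adjustment could recover.** If the planning variance of 26.99 includes the age effect, the part due to age band is f(1 − f) × (band difference)².

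- At 5 degrees: 0.21 × 25 = 5.25 to 0.25 × 25 = 6.25, which is 19% to 23% of 26.99.
- At 2.5 degrees: 0.21 × 6.25 = 1.31 to 0.25 × 6.25 = 1.56, which is 5% to 6%.

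If age has little effect on flexion, both the shift and the gain are close to nil.

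**Arm sizes, for the objection below.** If allocation were simple 1:1, the smaller of two arms totalling 74 would be below 33 with probability 29.5% (binomial). After 10% random dropout, at least one arm would end below 33 completers with probability 81%. With a perfect 37:37 split it is already 52%. Power by noncentral t is 0.794 at 33/33, 0.791 at 30/36 and 0.785 at 28/38. Averaged over simple randomisation it is 0.788 against 0.794 at 66 completers, and 0.834 against 0.839 at 74.

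**The case against.** Unstratified randomisation is valid. It does not bias the comparison, and the ordinary standard error already allows for chance imbalance. An age interaction analysis does not need stratified allocation. The plan says only that age may have an influence, and the list of variables that can trigger ANCOVA is open, so age could be included. On the figures above, a 15-point gap is absent in at least 80% of lists. All of this stands, and it makes the point one of precision and interpretability. It does not rescue the main analysis, because 2.11 states the order of analyses: unadjusted first, with adjustment as a conditional sensitivity analysis. That is stated text, not a detail that a condensed article has left out.

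A reader might go further and infer that allocation is unrestricted, so that the requirement in 2.10, "which was calculated to require 33 patients in each group", would often be missed. The documents do not support this. Section 2.4 does not say whether blocks are used, a computer-generated table can be blocked, and an article may leave block details to the full protocol. Even if allocation were simple, unequal arms would cost only about half a point of power on average, since power depends mainly on the total. Most of the shortfall below 33 completers (52 of the 81 percentage points) would remain with perfectly equal arms and comes from the dropout allowance.

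A reader might also ask for stratification by district, since recruitment covers Hongkou and Yangpu. Nothing in the article calls district prognostic.

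**Conclusion.** The point holds in a limited form. The trial is evidently not stratified, age is named as a possible influence, and the main range-of-motion comparison ignores it unless an undefined imbalance trigger is met, and then only as a sensitivity analysis. The chance of an age-band gap of 15 points or more is about 16% to 20%, assuming 30% to 50% of patients are under 40. Such a gap would move the result by about 10% to 21% of the planned difference if the bands differ by 2.5 to 5 degrees, which is also assumed. The consequence is chance imbalance and lost precision. There is no systematic bias, and no established shortfall in arm size.

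**What to change.** In 2.11, pre-specify the primary comparison as an ANCOVA of lumbar flexion range of motion with treatment group and age, applied whether or not imbalance is seen. The t-test or rank-sum test can stay as an unadjusted supporting analysis. Fix this before outcome data are examined by arm. It needs a short amendment and no new data, because age is already collected.

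In 2.4, state the allocation method. Section 2.3 dates the start of enrolment to September 2023, so the rest applies only if allocations remain to be made. In that case, use permuted blocks of varied size stratified by age at the 40-year cut that 2.11 already mentions, and keep that stratum in the model. The independent person and opaque envelopes stay as planned. The cost is a new list and two envelope stacks instead of one, covered by the same amendment. If enrolment is complete, the analysis change alone is enough.

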### Interventions

2.5

#### WQXs

2.5.1

The movements of tiger play (tiger lift, tiger pounce), deer play (necked deer, necked deer) and bear play (bear shake, bear movement) are selected as the basis for the exercise routine design.

The initial phase consists of a 5-min preparatory warm-up session, followed by a 20-min simplified WQXs exercise targeting the core muscles of the low back and abdomen. Subsequently, the third stage involved a 5-min relaxation training component within the simplified WQXs regimen. In the simplified WQXs training for the core muscles of the lumbar and abdominal regions, a standing and moving position is used, Perform 3 sets of each movement, with 15 repetitions per set, maintaining each repetition for 5 s, and allow a 30 s rest interval between sets. A course of 5 sessions/week, combined with health education and a 2-day break between sessions, The study observation period spanned 24 weeks, comprising a 1-week intervention phase followed by follow-up assessments at weeks 6, 12, 18, and 24 (Figure 2).

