#### MT

2.5.2

The MT method of treatment (application of prone stretching, stretching and relaxation, rotation and relaxation in the stretching position, and continuous rotation in the flexion position) is performed. The method (based on treatment techniques such as prone extension, extension release, extension rotation release, and continuous rotation in flexion) is performed for 10 min, Perform 3 sets of each movement, with 15 repetitions per set, maintaining each repetition for 5 s, and allow a 30 s rest interval between sets. It is advisable to ensure that the interval between each action does not exceed 30 min. 40 min of exercise treatment and health lectures are given to the patients to enhance their compliance. A course of 5 sessions/week, combined with health education and a 2-day break between sessions.

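### The stated sets, repetitions and holds do not fit the stated session lengths, and the efficacy rule counts in an undefined cycle that may be impossible to exceed in the stated 1-week intervention

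*Protocol article*

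**What the plan says.** **Movements and time, WQXs (section 2.5.1).** The routine is built on six entries, with the two deer entries printed identically: "The movements of tiger play (tiger lift, tiger pounce), deer play (necked deer, necked deer) and bear play (bear shake, bear movement) are selected". A 5-min warm-up is "followed by a 20-min simplified WQXs exercise targeting the core muscles of the low back and abdomen", and then by 5 min of relaxation. The volume is given as "Perform 3 sets of each movement, with 15 repetitions per set, maintaining each repetition for 5 s", with 30 s of rest from one set to the next.

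**Movements and time, MT (section 2.5.2).** Four techniques are named and given 10 min. The sets, repetitions, hold and rest are the same as for WQXs. The section also mentions 40 min of exercise treatment and health lectures.

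**Frequency (both sections).** "A course of 5 sessions/week, combined with health education and a 2-day break between sessions".

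**Duration and visits.** Section 2.5.1: "The study observation period spanned 24 weeks, comprising a 1-week intervention phase followed by follow-up assessments at weeks 6, 12, 18, and 24". Section 2.6 lists the follow-up evaluations at 0, 6, 12 and 24 weeks, without week 18.

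**Efficacy rule (section 2.11).** After discontinuation for adverse reactions, "those who have participated in more than 1 cycle of exercise should be counted for efficacy". The article does not define a cycle. Section 2.6 uses the word for the whole assessment period.

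**The concern.** Sections 2.5.1 and 2.5.2 each fix both a time and a volume for the same block of exercise, and the two do not agree. A therapist has to give up one of them, and the text does not say which. MT is the only planned difference between the arms, so the mismatch there bears directly on what the trial tests.

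The second issue concerns the analysis. A rule on who is counted for efficacy is written in a unit without a definition. On the two meanings that the article's own text suggests, the threshold cannot be passed within the intervention phase or observation period stated. The visit weeks also differ between sections, so the timeline that would settle the question is not fixed in the text.

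**Working it through.** **1. The plan's own total.** Warm-up 5 + WQXs 20 + relaxation 5 + MT 10 = 40 min. This matches the 40 min in section 2.5.2, so the stated block lengths agree with one another.

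**2. Time per movement from the stated volume.** Holds: 3 × 15 × 5 s = 225 s = 3.75 min. Rests between three sets: 2 × 30 s = 60 s. Total: 285 s = 4.75 min. No time is allowed for changing movement.

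**3. Number of movements × time per movement.**

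| Block | Movements | Holds only | With rests between sets | Stated |
|---|---|---|---|---|
| WQXs | 6 (as listed) | 22.5 min | 28.5 min | 20 min |
| WQXs | 5 (deer entry counted once) | 18.75 min | 23.75 min | 20 min |
| WQXs | 4 | 15.0 min | 19.0 min | 20 min |
| MT | 4 (as listed) | 15.0 min | 19.0 min | 10 min |
| MT | 3 | 11.25 min | 14.25 min | 10 min |
| MT | 2 | 7.5 min | 9.5 min | 10 min |

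With the stated rests, the blocks hold the stated volume only for four or fewer WQXs movements and two or fewer MT techniques. For the full lists, the holds alone already overrun both blocks. Adding up the same assumption gives 5 + 28.5 + 5 + 19 = 57.5 min for a combined session against 40 min. This is a consequence of the two overruns and not further evidence.

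**4. Cycle against duration.** The intervention phase is 1 week, and the only exercise unit described is a weekly course of 5 sessions.
- Cycle = weekly course: at most 1 week ÷ 1 week = 1, so more than one cannot occur.
- Cycle = whole assessment period (section 2.6): at most 1, so more than one cannot occur.
- Cycle = one session: up to 5, so the rule works, but the article does not say this.

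**5. Break between sessions.** Read literally, five sessions with two free days between each span 5 + 4 × 2 = 13 days, and a 7-day week holds at most three (days 1, 4 and 7). Read as five days on and two off, 5 + 2 = 7 days and there is no conflict.

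**6. Visit weeks.** Section 2.5.1: 6, 12, 18, 24. Section 2.6: 0, 6, 12, 24. Week 18 is in one list only.

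**7. Sample size, as a check on reach.** Section 2.10 gives 46.20 ± 5.25 and 42.59 ± 5.14. The difference is 3.61 and the mean variance (5.25² + 5.14²)/2 = 26.99. With two-sided 0.05 and 80% power (power is assumed here), n = 2 × (1.960 + 0.842)² × 26.99 / 3.61² ≈ 32.5, so 33 per group. Then 33/0.90 = 36.7, so 37 per group and 74 in total. The plan's figures reproduce and do not depend on the schedule.

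**The case against.** The time calculation assumes that every listed item is done in full at every session. Section 2.5.1 calls the movements a basis for designing the routine, one of the two MT sentences offers its techniques as examples, and the Background describes MT as personalized. A therapist manual could select fewer items, and an article condenses the full protocol. This softens the MT part somewhat. It does not remove the point: the volume is set for each movement, the other MT sentence names the four techniques without qualification, and nothing in the text reduces the lists. The mismatch lies between figures that are printed, so it is not a matter of omitted detail.

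Several stronger readings are tempting and should not be made:
- **That 5 sessions a week is impossible.** Five days on and two off is a natural reading. Only the wording needs correcting.
- **That the 30-min limit in section 2.5.2 contradicts the 30 s rest.** "It is advisable to ensure that the interval between each action does not exceed 30 min" is an upper limit. A 30 s rest satisfies it, and the two concern different intervals. It is oddly loose, but it is not a contradiction.
- **That nobody can be counted for efficacy.** The rule does not say that only those beyond one cycle are counted. It concerns people who discontinue, and the conflict depends on what a cycle is.
- **That the half-of-data rule in section 2.11 conflicts with a 1-week phase.** No conflict is shown, because the data meant may be the scheduled assessments.

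Figure 2 is not available here and may clarify the timeline. It could not make the printed figures in the text agree.

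**Conclusion.** The point holds in two parts of different strength.

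The firm part is arithmetic. For the movements as listed, the stated volume needs 28.5 min against 20 min for WQXs (23.75 min if only five are distinct) and 19 min against 10 min for MT, which is 1.9 times the stated time. It rests on each listed movement being done at the stated sets, repetitions and holds in each session.

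The conditional part is the efficacy rule. If a cycle is the weekly course or the whole assessment period, the threshold cannot be passed. If it is a single session, the conflict disappears, but the article does not give that meaning.

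A reader might infer that the treatment effect becomes uninterpretable. The document does not support that: randomisation still allows a comparison of the arms as assigned, the WQXs component is common to both, and the sample size is unaffected. What remains unclear is which regimen that comparison evaluates and who enters the efficacy analysis.

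**What to change.** The sponsor, with its clinical team, should reconcile sections 2.5.1, 2.5.2, 2.6, 2.11 and Figure 2 so that:
- the exercise volume and the block lengths agree in both intervention sections, including whether all listed movements are done at each session and whether the repeated deer entry is one movement or two;
- the intervention duration is stated once and used throughout;
- one list of visit weeks stands, with week 18 either in or out;
- the wording on the two-day break is corrected if five days on and two off is meant;
- the efficacy rule in section 2.11 is restated in a defined unit that the reconciled schedule makes attainable.

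The statistician can then define adherence, and which visits fall during or after treatment, from the reconciled schedule. Which figures are right is for the sponsor to decide, and no dose or duration is proposed here. The cost is a clarifying amendment and a check of the therapist manual. No new data are needed and the sample size does not change.
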